**Methods/Design:**

The randomized controlled trial will be conducted with 220 women who have a BMI > 18.5 (American IOM cut-off for normal weight), are 18 years of age or older, English speaking, no history of disordered eating or diabetes and are less than 18 weeks gestation at recruitment. Women will be randomly allocated to either a specialized HC intervention group or an Education Alone group. Our specialized HC intervention has two components: (1) one-on-one sessions with a Health Coach, and (2) two by two hour educational group sessions led by a Health Coach. Women in the Education Alone group will receive two by two hour educational group sessions with no HC components. Body Mass Index, waist circumference, and psychological factors including motivation, readiness to change, symptoms of depression and anxiety, and body dissatisfaction will be assessed at baseline (14-16 weeks gestation), and again at follow-up: 32 weeks gestation, 6 weeks, 6 months and 12 months postpartum.

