### Participants

Participants will be 220 pregnant women. Women will be able to participate if they provide informed consent, have a BMI > 18.5 (US IOM cut-off for normal weight), are 18 years of age or older, English speaking and less than 18 weeks gestation at recruitment with no history of disordered eating or diabetes. After baseline assessment, women who meet the eligibility criteria will be randomly allocated to either the HC Intervention group (*n *= 110) or the Education Alone group (*n *= 110). A coded, double-blinded, variable-length permuted blocks randomized treatment allocation schedule, produced by computer algorithm, will be used.

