### Power, sample size, and retention

Given that the primary outcome of the study is maternal BMI, we aim to detect a clinically relevant difference in BMI of 0.8 kg/m^2 ^at 12 months postpartum. This difference is in accordance with the New Life (style) RCT that is currently being conducted in the Netherlands [63], that targets weight advice, weight development, nutrition and physical activity habits, but fails to target motivational variables, behavior-change assistance or psychological factors, such as depressive symptoms, anxiety symptoms, and body image. Consequently, the required *n *to detect this difference with 80% power at *α *= 0.05 and a standard deviation of 2 kg/m^2^, is 110 women per group; we have adopted this SD because we will also be measuring weight objectively at baseline and 12 months postpartum, removing any bias associated with self-report. Allowing for attrition of 20%, we will recruit 264 women and randomly assign 132 women into the HC Intervention and 132 women into the Education Alone control group. Our estimate of a drop-out rate is conservative and based on our previous large longitudinal studies with pregnant women and multiple time points [21,23,64]. As in our previous longitudinal pregnancy studies, this attrition rate of 20% takes into consideration that 5-7% of women may be diagnosed with gestational diabetes, which we expect to occur at 24-26 weeks; these women will therefore not affect the intervention, because we will over sample. A permuted blocks randomized treatment allocation schedule, produced by computer algorithm, will be used for the randomization process. To facilitate retention, we will build rapport with the participants through a study website, a regular newsletter, telephone support and advanced notification of assessments.

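### The protocol gives two different numbers to randomise, 220 and 264; at 220, its own 20% attrition leaves about 75% power, not 80%

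*Protocol article*

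**What the plan says.** The Power, sample size, and retention section starts from BMI as the outcome ("Given that the primary outcome of the study is maternal BMI") and aims to detect "a clinically relevant difference in BMI of 0.8" kg/m² at 12 months postpartum. With 80% power, alpha 0.05 and "a standard deviation of 2" kg/m², it arrives at 110 women per group. It then allows for 20% attrition and states: "we will recruit 264 women and randomly assign 132 women into the HC Intervention and 132 women into the Education Alone control group".

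Three other places give the smaller total:

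- Abstract, Methods/Design: "The randomized controlled trial will be conducted with 220 women".
- Participants: "Participants will be 220 pregnant women", followed by random allocation after baseline assessment to two groups of n = 110.
- Table 1: the column heads show n = 110 for each group, in a table that begins with the baseline assessment at 14-16 weeks.

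**The concern.** The Participants section ties 110 per group to the act of random allocation. The power section ties 132 per group to that same act and uses 110 as the requirement before attrition is allowed for. Both cannot be the number randomised. The likeliest explanation is that the pre-attrition requirement was carried into the Abstract, the Participants section and Table 1.

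The number randomised determines when recruitment stops, and it is the denominator for the intention-to-treat analysis that the Analyses section promises. A team working from the Participants section would stop 264 − 220 = 44 women short of the power section's target. It would then have no allowance for loss to follow-up or for the gestational diabetes cases that the power section says over-sampling will cover.

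**Working it through.** **Inputs, all from Power, sample size, and retention:** difference δ = 0.8 kg/m²; SD σ = 2 kg/m²; alpha 0.05; power 80%; attrition 20%. The protocol does not say whether alpha is one- or two-sided; two-sided is assumed here by convention. The standardised difference is d = 0.8/2 = 0.4.

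**Step 1: the protocol's own 110 per group.** For two means,

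n per group = 2 × (z₀.₉₇₅ + z₀.₈₀)² / d² = 2 × (1.960 + 0.842)² / 0.16 ≈ 98.1, so 99.

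The t-test version gives 99.08, so 100. The stated 110 is not reproduced. One-sided alpha gives 78, 85% power gives 113 and 90% power gives 132 (normal approximation), so none of these variants gives it either. The discrepancy is on the safe side: 110 evaluable per group gives 84% power.

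**Step 2: the attrition allowance.** 132 = 110 × 1.2. Multiplying by 1.2 covers a loss of 1 − 110/132 = 16.7%, not 20%. Keeping 110 after a 20% loss needs 110/0.8 = 137.5, so 138 per group (276 in total).

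**Step 3: evaluable women under each total.**

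- 220 randomised: 110 × 0.8 = 88 per group.
- 264 randomised: 132 × 0.8 = 105.6 per group.

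**Step 4: power.** The normal approximation is Φ(d × √(n/2) − 1.960). For n = 88 this is Φ(0.4 × √44 − 1.960) = Φ(0.693) = 75.6%. The t-test figures, from the noncentral t distribution, are close to it:

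| Randomised | Attrition | Evaluable per group | Power, normal | Power, t-test |
|---|---|---|---|---|
| 220 | 20% | 88 | 75.6% | 75.1% |
| 264 | 20% | 105 (105.6 rounded down) | 82.6% | 82.2% |
| 220 | none | 110 | 84.3% | 84.0% |

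**Step 5: how much loss each total can absorb.** Since 99 to 100 evaluable women per group give 80% power, 220 randomised tolerates a loss of 1 − 100/110 = 9% to 1 − 99/110 = 10%. 264 randomised tolerates 1 − 100/132 = 24% to 1 − 99/132 = 25%. The planned 20% lies between the two ranges.

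**The case against.** The strongest reply is that the design as calculated is adequate. The only section that derives the sample size randomises 264, which keeps power above 80% after attrition, and no passage claims 80% for 220 randomised with 20% lost. That is fair: the 75% is what follows if 220 is the operative number. It does not remove the conflict, because the Participants section states 110 per group as the number allocated.

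It can also be said that only the Participants section allocates 110 per group in so many words. The Abstract gives a total without group sizes, and the Table 1 heads do not say whether n means randomised or evaluable. This is true, but one explicit statement is enough for a contradiction, and the other two agree with it.

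The size of the shortfall is open to argument too:

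- The protocol calls its drop-out estimate conservative. With 10% attrition, 220 leaves 99 per group and power of 80.0%. But 20% is the stated planning figure.
- Covariate adjustment, planned in Analyses, would restore 80% at 88 per group if the covariates explained about 12% of the outcome variance. But the listed covariates do not name baseline BMI, and the calculation claims no such gain.
- A one-sided test would give 84% at 88 per group. But nothing in the article indicates one, and it would need only 78 per group, further from the stated 110.

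Multiple imputation keeps every woman in the analysis, but it does not by itself bring back the outcome information lost with the drop-outs.

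**Conclusion.** Wrong as written. The protocol states two incompatible numbers to randomise, and nothing in it reconciles them. At 220, its own inputs give about 75% power, so a type II error of about 25% instead of the planned 20%; at 264, power is about 82% and the 80% claim holds. The figures rest on a two-sided alpha of 0.05, an unadjusted comparison of two means and the full 20% attrition. The shortfall is about 5 percentage points, and it is smaller if fewer women are lost or if covariates explain a useful share of the variance. The point still has to be settled, because it fixes when recruitment ends.

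**What to change.** Choose one total and use it throughout.

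- **Preferred:** put 264 (132 per group) into the Abstract, the Participants section and the Table 1 column heads, to match the power section.
- **Alternative:** keep 220 (110 per group), change the recruitment sentence in the power section, and restate the power there as about 75% with 88 evaluable women per group.

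In either case, say whether 110 means randomised or evaluable women, and state that alpha is two-sided if it is. If 264 is kept, correct the power section's arithmetic in the same edit: the stated inputs need 99 to 100 evaluable women per group, and 264 leaves about 105 per group after a 20% loss, which is enough for 80% power although below the stated 110. If 110 evaluable is to be kept as the requirement, the total consistent with 20% attrition is 276.

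If 264 is already the working target, the cost is wording only. If recruitment has been organised around 220, moving to 264 means 44 more women, 22 of them receiving individual coaching. Keeping 220 costs only a less favourable stated power.

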### Excessive weight gain during pregnancy

Excessive weight gain in pregnancy is a common health-related problem in Western countries [3]. Women who gain excessive weight during pregnancy have an increased risk of postpartum obesity in themselves and their children [2,4]. Furthermore, 20% of women retain at least 5 kg of gestational weight gain at 6-18 months post birth [5,6], and this weight retention is a strong predictor of maternal overweight and obesity a decade or more after birth [7].

In 2009 the United States (US) Institute of Medicine (IOM) published revised guidelines for how much weight a woman should gain during pregnancy and highlighted the importance of intervention in pregnancy to prevent both postpartum weight retention and childhood obesity [8]. The US IOM recommends that women with a normal weight (Body Mass Index, BMI, of 18.5-24.9 kg/m^2^) should gain between 11-16 kg during their pregnancy; women who are overweight (BMI of 25-29.9 kg/m^2^) should gain 7-11 kg, and obese women (BMI of 30 kg/m^2 ^and above) should gain between 5 to 9 kg [8]. Women who are underweight (BMI less than 18.5 kg/m^2^) should gain between 13 to 18 kg during pregnancy [8]. Excessive gestational weight gain (GWG) is defined as weight gain above these recommended guidelines. The specific cost of excessive gestational weight gain is related to ensuing maternal health problems and fetal outcomes [9], such as preeclampsia [10], maternal hyperglycemia [11], complications with labor/delivery [12,13], infant macrosomia [12,13], late fetal death [14], birth defects [15], and an increased risk of caesarean [10].

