### Analyses

We will adhere to 'intention-to-treat' principles following CONSORT Statement guidelines to prevent introduction of systematic bias [48]. As such, baseline data will be secured prior to treatment allocation, missing values will be scrutinized to check for non-random distribution and primary analyses will be executed twice: once using observed data, and once using multiple imputation under multivariate normal assumptions using methods given by Schaffer [65], so that all participants will be analyzed in their allocated condition. Analyses of covariance (with "other relevant variables" from above as covariates) will test the between group differences in the primary and secondary outcomes at each assessment time point and across time points. The confounder-adjusted analysis of the proportion of women returning to pre-pregnancy weight at 12 months post birth in each group will be tested using a logistic regression model. The second hypothesis will be tested using hierarchical regressions and path analysis. In addition, to further clarify the direction of effects between two variables across multiple time points, cross-lagged panel analyses will be conducted, e.g., to determine whether the level of maternal activity/depressive symptoms is a cause or consequence of higher BMI. Finally, the interview transcripts will be analyzed using elements of phenomenology and thematic content analysis to determine barriers to adopting healthy behaviors for weight management and the support or resources that women find most useful in achieving their gestational weight gain/postpartum weight loss goals [25,66].

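### Women diagnosed with gestational diabetes after randomisation are budgeted as attrition, which conflicts with the commitment to analyse everyone as allocated

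*Protocol article*

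**What the plan says.** The Protocol article, section Power, sample size, and retention, aims to detect a "clinically relevant difference in BMI of 0.8" kg/m² at 12 months postpartum and concludes that the required number "is 110 women per group". It continues: "Allowing for attrition of 20%, we will recruit 264 women", 132 per arm. The same paragraph explains that the 20% already takes account of the 5-7% of women who may be diagnosed with gestational diabetes, expected at 24-26 weeks, and that "these women will therefore not affect the intervention, because we will over sample".

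The Analyses section commits to intention-to-treat. The primary analyses are to be run twice, once on observed data and once with multiple imputation, "so that all participants will be analyzed in their allocated condition".

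The Participants section bars women with a history of diabetes at entry. It says nothing about a diagnosis made later.

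**The concern.** A woman diagnosed with gestational diabetes can still be weighed before delivery and at 12 months. Her diagnosis uses up attrition allowance only if the trial stops collecting or using her data. Likewise, over-sampling can keep these women from having an effect only if they drop out of the comparison. Read that way, the sample-size section plans a loss defined by an event after randomisation, while the Analyses section promises that no one is lost from her arm.

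The event need not be independent of allocation. The Background lists, among the problems related to excessive gestational weight gain, conditions "such as preeclampsia [10], maternal hyperglycemia [11], complications with labor/delivery". Excessive gain is what the coaching is meant to prevent, so on the article's own account the diagnosis could differ by arm and could be related to the BMI outcome. Removing women on such an event can make the arms non-comparable, and recruiting more women at the start does not repair that.

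**Working it through.** **Order of events** (Overall study design, Participants, Table 1)

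- 14-16 weeks: baseline assessment, followed by randomisation.
- 16-18 weeks: first one-on-one coaching session.
- 20 and 22 weeks: group sessions.
- 24 weeks: second one-on-one session.
- 24-26 weeks: expected diagnosis.

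The women concerned are therefore eligible, randomised and already exposed to most of the scheduled sessions.

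**The plan's own figures.** The inputs are a difference of 0.8, "with 80% power at" α = "0.05 and a standard deviation of 2" kg/m². Two-sided testing is assumed, since the article does not say.

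- n per group = 2 × (1.960 + 0.842)² × 2² / 0.8² = 98.1, so 99 (100 by the t-test version). The stated 110 is not reproduced. It is on the conservative side and gives about 84% power.
- 132 = 110 × 1.20. Dividing by the retained fraction would give 110 / 0.80 = 137.5, so 138.
- At 20% loss, 132 × 0.80 = 105.6 per group remain, with about 83% power.

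Power is therefore not the problem. The issue is bias and internal consistency.

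**Women concerned.** 264 × 0.05 = 13.2 and 264 × 0.07 = 18.5, so about 13-18 women, or about 7-9 per arm.

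**Possible bias.** Let g₀ and g₁ be the proportions diagnosed in the education and coaching arms, and D the excess in 12-month BMI of diagnosed women, taken as equal in both arms. With everyone analysed, the between-arm difference contains (g₀ − g₁) × D. With diagnosed women left out, that part disappears. Neither g₀ − g₁ nor D is in the article, so these are assumptions:

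- Equal incidence: 0 × D = 0.
- 5% v 4%, D = 2: 0.01 × 2 = 0.02 kg/m²; 0.02 / 0.8 = 2.5% of the target.
- 7% v 3.5%, D = 3: 0.035 × 3 = 0.105 kg/m²; 13% of the target.
- 7% v 3.5%, D = 5: 0.035 × 5 = 0.175 kg/m²; 22% of the target.

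A second mechanism gives much the same size. Suppose coaching averts the diagnosis but those women stay heavier. They then remain in the coaching arm while their counterparts are removed from the other: 0.035 / 0.965 × 5 = 0.18 kg/m². If coaching lowers incidence and D is positive, both mechanisms shrink the apparent benefit. If incidence were higher under coaching, the direction would reverse.

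**Numbers if these women are kept.** Taking the 5-7% out of the 20% leaves 13-15% other loss.

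- 132 × 0.87 = 114.8 and 132 × 0.85 = 112.2 per group, with power of about 85-86%.
- To end with 110 per group: 110 / 0.87 = 126.4, so 127; 110 / 0.85 = 129.4, so 130. Both lie within 132.

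**The case against.** The strongest reply is that nothing in the article withdraws or excludes these women. The sentence stands in a sample-size paragraph, which may simply budget for missing outcomes. The Analyses section governs the analysis and would impute what is missing, in the allocated arm. Detailed withdrawal rules may also sit in a fuller protocol that is not shown.

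Part of this stands. A reader might infer that the plan states an exclusion, but it does not; exclusion is an inference from how the allowance is justified. A reader might also infer one-for-one replacement, but the text describes only an up-front increase from 110 to 132 per arm.

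The imputation argument does not remove the conflict. The observed-data run of the primary analysis would omit women whose outcomes were not collected. If outcomes were systematically not collected after the diagnosis, no diagnosed woman would have an observed 12-month BMI, and imputation would have to borrow from women without the diagnosis. Nor does the point rest on missing detail: the article makes a positive statement about how these women are handled, and that statement does not fit its own analysis commitment.

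**Conclusion.** The point holds as a conflict between two sections. Counting a post-randomisation diagnosis as attrition, and dismissing it because of over-sampling, does not fit a commitment to analyse all participants as allocated. It concerns about 13-18 of 264 women, on the article's own 5-7%.

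The size of the bias is not established. It is about zero if incidence, and the BMI gap of diagnosed women, are the same in both arms. It runs from roughly 0.02 to 0.18 kg/m² under the assumed differences of 1 to 3.5 points and gaps of 2 to 5 kg/m². A reader might take the upper part of that range, 13-22% of the target, as the expected loss. The documents do not support this: it needs a halving of diagnoses and a gap of 1.5 to 2.5 times the planning SD of 2, and neither has a source in the article. A reader might also infer that these are the women in whom excess gain and retention matter most. The article does not say so.

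**What to change.** Reconcile the two sections.

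- In Power, sample size, and retention, delete the over-sampling rationale and let the attrition allowance cover true loss to follow-up only.
- In Analyses, state that women diagnosed with gestational diabetes after randomisation remain in follow-up and in the primary analysis in their allocated arm.
- Label any analysis without them as a sensitivity analysis.

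This concerns data collection and analysis only; it says nothing about how these women are managed clinically.

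The cost is wording plus 12-month follow-up of about 13-18 women already enrolled. No extra recruitment is needed: 127-130 per group suffices for 110 completers at 13-15% loss, against 132 planned. If the full 20% is kept for true loss, 132 leaves 105.6 per group, still above the 99-100 that the stated inputs require. These figures use the 264 target. The Participants section and Table 1 give 110 per group, which would contain no over-sampling at all; that is a separate discrepancy. Under either target, keeping these women can only add to the number analysed.

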### Analyses

We will adhere to 'intention-to-treat' principles following CONSORT Statement guidelines to prevent introduction of systematic bias [48]. As such, baseline data will be secured prior to treatment allocation, missing values will be scrutinized to check for non-random distribution and primary analyses will be executed twice: once using observed data, and once using multiple imputation under multivariate normal assumptions using methods given by Schaffer [65], so that all participants will be analyzed in their allocated condition. Analyses of covariance (with "other relevant variables" from above as covariates) will test the between group differences in the primary and secondary outcomes at each assessment time point and across time points. The confounder-adjusted analysis of the proportion of women returning to pre-pregnancy weight at 12 months post birth in each group will be tested using a logistic regression model. The second hypothesis will be tested using hierarchical regressions and path analysis. In addition, to further clarify the direction of effects between two variables across multiple time points, cross-lagged panel analyses will be conducted, e.g., to determine whether the level of maternal activity/depressive symptoms is a cause or consequence of higher BMI. Finally, the interview transcripts will be analyzed using elements of phenomenology and thematic content analysis to determine barriers to adopting healthy behaviors for weight management and the support or resources that women find most useful in achieving their gestational weight gain/postpartum weight loss goals [25,66].

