### Measures

Women will meet with researchers at 14-16 weeks gestation to collect demographic information (including pre-pregnancy BMI) and obtain anthropometric measurements (BMI and waist circumference). Women will also be given a copy of the US IOM gestational weight gain guidelines [9] and baseline measures of motivation, importance, confidence and readiness to adopt healthy lifestyle behaviors for weight management, perceived social support, depressive symptoms, body dissatisfaction, dietary habits and physical activity will be collected by questionnaire. Follow-up assessment of measures will take place at 32 weeks gestation, and at 6 weeks, 6 and 12 months post birth, with the exception of anthropometric measures which will be assessed at baseline and at 12 months post birth.

All measures in the questionnaire, with the exception of the first 14-16 week assessment session, will be collected in one of two ways: (1) via self-report questionnaires sent to the home of women with a request to return completed questionnaires (that will take no more than 30 minutes to complete) to the researchers in reply-paid envelopes provided to them; (2) by researcher interview over the phone. Women will be able to choose the method of data collection that suits them best. Anthropometric measures will be obtained in person by trained research staff.

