### Primary outcomes

#### BMI

Height will be measured by researchers with a stadiometer at the first and last assessments (14-16 weeks gestation and 12 months postpartum) for both groups. Women will be weighed each time wearing light clothing and no shoes. Pre-pregnancy weight will be based on self-report; weight at 14-16 weeks gestation and 12 months postpartum will be measured by the researchers using electronic scales. Height and weight measurements will be used to calculate BMI (kg/m^2^). At all other assessment time points, women will be encouraged to consult with their healthcare professional to provide additional objective weight measurements (including the last weight reported prior to delivery), and in the postpartum we will ask women to be weighed at their Maternal and Child Health appointment. Women will record these measurements in a 'weight passport' provided by researchers.

Waist circumference will be measured by trained researchers using a standard tape measure when height and weight measurements are obtained.

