### Secondary outcomes

All the measures below will be measured at each of the assessment time points noted in Table 1.

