#### Other relevant variables

Other variables will be included to ensure comprehensive assessment and will be examined as secondary, or covariate variables. These include parity, socioeconomic status, substance use, healthcare resource-use, perceived social support, coping style and appraisal of stressful events, beliefs about gestational weight gain, labor experiences (e.g., length, type), breast-feeding experiences, birth weight and delivery date.

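### The stated ANCOVA covariates omit each outcome's own 14-16 week value, so between-arm comparisons of waist and the questionnaire outcomes are less precise than the data allow

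*Protocol article*

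**What the plan says.** The protocol article's Analyses section sets one model for the arm comparisons: "Analyses of covariance (with 'other relevant variables' from above as covariates) will test the between group differences in the primary and secondary outcomes". It applies this model at each assessment and also across assessments.

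The covariate set is fixed by reference to the section Other relevant variables. That section gives the set its role, "Other variables will be included to ensure comprehensive assessment and will be examined as secondary, or covariate variables", and begins the list: "These include parity, socioeconomic status, substance use, healthcare resource-use, perceived social support, coping style and appraisal of stressful events". The rest of the list is beliefs about gestational weight gain, labor, breast-feeding, birth weight and delivery date.

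The baseline values of the outcomes are collected elsewhere in the plan:

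- The Measures section records at 14-16 weeks "baseline measures of motivation, importance, confidence and readiness to adopt healthy lifestyle behaviors for weight management", and adds "perceived social support, depressive symptoms, body dissatisfaction, dietary habits and physical activity will be collected by questionnaire".
- The Secondary outcomes section states "All the measures below will be measured at each of the assessment time points noted in Table 1", and the first time point in Table 1 is the 14-16 week assessment.
- For waist, the Measures section refers to "anthropometric measures which will be assessed at baseline and at 12 months post birth", and the BMI section says "Waist circumference will be measured by trained researchers using a standard tape measure when height and weight measurements are obtained".
- The Participants and Analyses sections both place baseline assessment before allocation.
- The Contour Drawing Rating Scales are the exception. The Body dissatisfaction section describes them as administered postpartum.

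**The concern.** An outcome's own pre-randomization value is usually among its strongest predictors. Here the plan goes beyond saying that covariates will be used: it says which ones, and the set it points to does not contain that value. The name of the group also sets it apart from the outcome measures described before it.

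At stake is the precision of the between-arm comparisons for motivation, readiness, confidence, mood, body attitudes, activity, diet and waist. Without the baseline term, residual variance is larger than it need be. A chance difference between arms at 14-16 weeks is also left in the estimate, with its uncertainty showing up as a wider interval. A real effect on these outcomes is then more easily missed.

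**Working it through.** **1. The plan's own figure.** The only sample size calculation, in Power, sample size, and retention, is for BMI: difference 0.8 kg/m², SD 2 kg/m², alpha 0.05 (two-sided assumed), 80% power, 110 per group.

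- n = 2 × 2² × (1.960 + 0.842)² / 0.8² = 98.1, so 99 per group; the t-based solution is 99.1, so 100.
- The stated inputs therefore do not return 110. With 110 per group, d = 0.8/2 = 0.4 gives 84.0% power (noncentral t, 218 df, noncentrality 0.4 × √(110/2) = 2.97).

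That mismatch is a separate matter. The article states no effect size or power target for the secondary outcomes or waist, so d = 0.4 and 110 per group serve below only as a reference case.

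**2. Effect of adding the baseline.** Let R² be the share of outcome variance that the listed covariates already explain, and ρ the correlation of baseline with follow-up (partial, given those covariates, when R² > 0). The residual variance is multiplied by (1 − R²)(1 − ρ²), so the effective standardized difference is d / √[(1 − R²)(1 − ρ²)]. Degrees of freedom spent on covariates are ignored. The documents give neither R² nor ρ; both are assumed.

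The baseline term alone removes ρ² of the residual variance: 9% at ρ = 0.3, 25% at 0.5, 51% at 0.7.

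Example, R² = 0 and ρ = 0.5: 0.4 / √0.75 = 0.462, power 92.7%.

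Power at d = 0.4, 110 per group:

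| R² of listed covariates | no baseline | ρ = 0.3 | ρ = 0.5 | ρ = 0.7 |
|---|---|---|---|---|
| 0 | 84.0% | 87.2% | 92.7% | 98.5% |
| 0.20 | 91.0% | 93.3% | 96.8% | 99.6% |

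The gain is about 3, 9 and 15 points in the first row, and about 2, 6 and 9 points in the second.

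**3. Other numbers analysed, R² = 0.**

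- 132 per arm less 20% = 105.6, about 106: 82.6% rises to 86.0%, 91.7% or 98.2%.
- 110 per arm (the number allocated in the Participants section) less 20% = 88: 75.1% rises to 79.0%, 86.1% or 95.9%.

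**4. If baseline enters only as a repeated measure.** A contrast in change from baseline has variance 2(1 − ρ) relative to a single follow-up. With 110 per group, d = 0.4 and R² = 0, this gives:

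- ρ = 0.3: 0.4 / √1.4 = 0.338, power 70%, below the 84% of follow-up alone.
- ρ = 0.5: 0.4 / √1 = 0.4, power 84%, no gain.
- ρ = 0.7: 0.4 / √0.6 = 0.516, power 97%, against 98.5% with baseline as a covariate.

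**The case against.** The strongest reply is that the article is a condensed account. It does not call the listed variables the sole covariates, its list opens as a list of examples, and the final model may be set out in an analysis plan that is not shown. It is true that nothing excludes the baseline value. But the article does more than stay silent: it names a covariate set, and an open list of variables other than the outcome measures does not naturally take in the outcome's own baseline. It would be too much to say that the plan forbids baseline adjustment; what can be said is that the stated specification leaves it out.

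Four further points stand and limit the finding.

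- **The planned comparisons are not of raw scores.** They are adjusted for variables such as social support and coping, which may predict mood. The comparator may therefore already be above 84%, which is why the second row of the table is needed.
- **The analysis across time points may carry 14-16 weeks as a repeated measure.** The article does not say so. This would not help the comparisons at single time points, and a change contrast is less efficient than covariate adjustment.
- **Hypothesis 2 is not tested by this ANCOVA.** The Analyses section assigns it to hierarchical regression and path analysis, and adds cross-lagged panel models, which by construction contain earlier values. A reader might infer that the test of Aim 2 is underpowered; the documents do not support that.
- **There is no bias.** A reader might also infer that chance baseline imbalance invalidates the comparisons. Randomization keeps them unbiased, and the standard error already allows for such imbalance.

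**Conclusion.** The point holds as an improvement available at almost no cost. The covariate set named in the Analyses section does not include the outcome's own 14-16 week value, although that value exists before allocation for waist and for the questionnaire outcomes other than the Contour Drawing Rating Scales. The consequence is lost precision in the between-arm comparisons at each time point, not an invalid analysis.

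The size cannot be fixed from the documents. In the reference case it runs from about 2 points of power (ρ = 0.3, R² = 0.20) to about 15 points (ρ = 0.7, R² = 0). This rests on an effect of 0.4 SD borrowed from the BMI calculation, on two-sided alpha of 0.05, on 110 women analysed per group, and on assumed values of ρ and R².

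**What to change.** In the Analyses section, state that each ANCOVA of an outcome measured at 14-16 weeks includes that outcome's own 14-16 week value as a covariate. State also that only assessments after allocation contribute to the group effect: 32 weeks, 6 weeks, 6 months and 12 months for the questionnaire outcomes, and 12 months only for waist. Where an outcome has no baseline, as with the Contour Drawing Rating Scales, say so.

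The cost is a sentence or two of wording and one degree of freedom per model, with no new data. The change does not settle whether items in the list that arise after allocation, such as labor, breast-feeding and birth weight, belong in the model; that is a separate question.
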